**Methods/design:**

The study design consists of a prospective randomised controlled three-armed clinical trial, which will be carried out at a specialist clinic for integrative medicine, to investigate the clinical effects of hydrotherapy on osteoarthritis of the knee or hip joint, in comparison with conventional physiotherapy.

One hundred and eighty patients diagnosed with osteoarthritis of hip or knee will be randomly assigned to one of three intervention groups: hydrotherapy, physiotherapy, and both physiotherapy and hydrotherapy of the affected joint. In the first group, patients will receive Kneipp hydrotherapy daily, with water applied in the form of alternate cold and warm thigh affusions (alternating cold and warm water stimulation is particularly relevant to the knee and hip regions).

Patients in the second group will receive physiotherapy of the hip or knee joint three times a week. Patients in the physiotherapy-hydrotherapy combination group will receive both joint-specific physiotherapy three times a week and alternate cold and warm thigh affusions every day. Follow-up assessments will be on three levels: clinical assessment by the investigator; subjective patient assessment consisting of a patient diary, and questionnaires on admission and at the end of the treatment phase; and a final telephone assessment by the external evaluation centre. Assessments will be made at baseline, after two weeks of inpatient treatment, and finally after a further ten weeks of follow-up. The primary outcome measure will be pain intensity of the affected joint in the course of inpatient treatment, judged by the patient and the investigator. Secondary outcomes include health-related quality of life and joint-specific pain and mobility in the course of the study. Statistical analysis of the results will be on an intention-to-treat basis.

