### Sample size

On the basis of the data from the pilot study, carried out between June 2008 and January 2009 at the Kneipp Clinic in Bad Wörishofen, Germany, on 30 patients with pre-existing osteoarthritis of the hip or knee, a sample size was estimated using G-Power 3.0.10 software (Faul F, Erdfelder E, Lang A.-G, and Buchner A, 2007). According to this calculation, a sample size of n = 180 patients will suffice to determine a possible interaction between the groups with respect to the primary outcome, with a statistical power of 95%.

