#### VI) Standardised survey of state of health based on the EQ-5D test

The EQ-5D test is a standardised international procedure for self-rating of the patient's health status. It is divided into a general descriptive part and a pain-related part. The five dimensions rated in the descriptive part are mobility, self-sufficiency, daily activities, pain or discomfort, and anxiety or depression; the pain section of the EQ-5D test consists of the visual analogue scale in the self-rating procedure. In contrast to the SF 36 and the AIMS2, a more exact rating of everyday activities and their disease-related restriction is possible. The inherent consistency and validity of the EQ-5D test have been well evaluated scientifically [39].

In the EQ-5D self-rating procedure, results will be recorded by the patients at the beginning of the study and at the end of the treatment phase; the external study evaluation centre will also collect data by telephone ten weeks later.

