### Statistical analysis

The data will be analysed using SPSS 15.0 (SPSS inc., 2006) software according to the intention-to-treat principle. Accordingly, all patients with valid values will be included in such a way that they remain in the groups in which they were originally randomised, irrespective of the treatment they actually received.

To check the homogeneity of the groups, a cross-sectional comparison of the baseline characteristics will be carried out. Various statistical procedures will be applied, depending on the scale level in each case. A factorial analysis of variance (one way ANOVA), if necessary with appropriate post hoc tests, will be carried out for the metric variables, body mass index (BMI), age and blood pressure, the scale values in SF-36, AIMS 2-F, visual analogue scale (VAS), and Lequesne index, the time required in the timed "up and go" test, and flexion and extension in the neutral-zero testing,. The nominal variables sex, affected joint (left, right, both sides) and the items of the EQ-5D will be analysed with chi-square tests. An analysis of variance with measured value repetition (ANOVA, repeated measures) will be performed for the longitudinal analysis of the primary outcome measure (VAS), and for the secondary outcome criteria (current mental health state, SF-36 sum scales, AIMS 2-SF scales, Lequesne index, time required in the timed "up and go" test, flexion and extension in the neutral-zero testing, and blood pressure) which are also metric variables. Should, contrary to expectations, there be any inhomogeneity between the groups with respect to important variables (baseline characteristics), adjustments will be made as far as possible in the scope of the longitudinal analysis. The secondary outcome measures on the nominal data level (EQ-5D) will be analysed with chi-square tests.

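### The EQ-5D items are self-ratings with ordered levels, but the protocol classes them as nominal and tests them with chi-square, losing efficiency and interpretability for one secondary outcome

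*Protocol article*

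**What the plan says.** All references are to the protocol article.

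- **Scale level and test at baseline (Statistical analysis).** "The nominal variables sex, affected joint (left, right, both sides) and the items of the EQ-5D will be analysed with chi-square tests". The EQ-5D items are grouped with two variables whose categories have no order.
- **Scale level and test as an outcome (same section).** "The secondary outcome measures on the nominal data level (EQ-5D) will be analysed with chi-square tests".
- **Rule for choosing the test (same section).** "Various statistical procedures will be applied, depending on the scale level in each case".
- **Nature of the items (secondary outcome VI, EQ-5D).** "The five dimensions rated in the descriptive part are mobility, self-sufficiency, daily activities, pain or discomfort, and anxiety or depression". The section calls the instrument a self-rating procedure. It does not state the number of response levels.
- **Timing (same section).** "results will be recorded by the patients at the beginning of the study and at the end of the treatment phase", with a further telephone assessment ten weeks later.
- **Longitudinal analysis (Statistical analysis).** Repeated-measures ANOVA is assigned to the VAS and to a list of metric secondary outcomes. The EQ-5D items are not on the list. The current mental health state scale, which the section on diagnostic and biometric evaluation attributes to the EQ-5D, is on it.
- **Baseline adjustment (same section).** It is foreseen only if the groups turn out inhomogeneous, and then "adjustments will be made as far as possible in the scope of the longitudinal analysis".

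**The concern.** A rating of how restricted or how much in pain a patient is has an order; sex and side of the affected joint do not. Putting the EQ-5D items in the same class as those two variables conflicts with the protocol's own rule that the method follows the scale level.

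Two things are lost. First, Pearson's chi-square gives the same value if the response levels are shuffled. It spreads its sensitivity over every pattern of difference instead of the one of interest, a shift towards better or worse. Its p-value is also not tied to a direction and comes with no effect estimate, although the research questions ask how effectively hydrotherapy influences quality of life and whether effects are comparable between arms. Second, each patient's starting level is recorded but appears to play no part in the comparison.

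The stake is a higher chance of missing a real shift in an EQ-5D dimension, and a weaker statement when one is found.

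**Working it through.** **1. The protocol's own figure.** Power is stated only for the primary outcome: "a sample size of n = 180 patients will suffice to determine a possible interaction between the groups with respect to the primary outcome", at 95%. Significance level, effect size, number of measurements and correlation are not given, so this can be neither reproduced nor refuted. At a two-sided level of 0.05 and two measurements it would imply an interaction effect size f of about 0.21 (correlation 0) down to 0.11 (correlation 0.7). No power figure is given for EQ-5D, so the rest is comparative.

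**2. Inputs.** From the document: 180 patients and three arms ("One hundred and eighty patients diagnosed with osteoarthritis of hip or knee will be randomly assigned to one of three intervention groups"). Assumed: 60 per arm, level 0.05, three response levels (five as a sensitivity case), a latent normal variable cut into levels, and a latent correlation of 0.3 to 0.7 between baseline and follow-up.

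**3. Cost of ignoring order, analytically.** For three arms and three levels, chi-square has (3−1)×(3−1) = 4 df; an ordinal test of three arms has 2 df. The noncentrality needed for 80% power is 9.63 with 2 df and 11.94 with 4 df.

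- Ratio: 11.94 / 9.63 = 1.24, so about 24% more patients are needed. Equivalently, 180 patients do the work of 180 / 1.24 ≈ 145.
- If the ordinal test has 80% power, the 4-df test has about 70%.
- Leaving out a baseline with observed correlation r multiplies the ratio by 1/(1−r²): 1.24/0.91 = 1.36 at r = 0.3, 1.24/0.75 = 1.65 at 0.5, and 1.24/0.51 = 2.43 at 0.7. These are upper bounds.

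**4. Simulation, graded shift of 0/0.25/0.5 SD, three levels, 4,000 runs per row.** The tests are Pearson chi-square, Kruskal-Wallis, and ANCOVA on ranks with the baseline item. The loss columns are differences in percentage points.

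| Levels (%) | Correlation | Chi-square | Rank test | Rank + baseline | Loss: order | Loss: both |
|---|---|---|---|---|---|---|
| 30/60/10 | 0.3 | 43.9% | 55.5% | 57.2% | 11.6 | 13.3 |
| 30/60/10 | 0.5 | 43.1% | 53.8% | 61.0% | 10.7 | 17.9 |
| 30/60/10 | 0.7 | 42.1% | 54.0% | 69.3% | 11.9 | 27.2 |
| 33/33/33 | 0.3 | 44.6% | 56.2% | 58.8% | 11.6 | 14.2 |
| 33/33/33 | 0.5 | 44.0% | 56.6% | 63.7% | 12.6 | 19.7 |
| 33/33/33 | 0.7 | 45.3% | 56.1% | 75.3% | 10.8 | 30.0 |
| 45/53/2 | 0.3 | 37.1% | 47.5% | 49.9% | 10.4 | 12.8 |
| 45/53/2 | 0.7 | 37.3% | 48.6% | 60.9% | 11.3 | 23.6 |

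The Monte Carlo standard error of each power is at most √(0.25/4000) = 0.8 points.

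**5. Simulation, 0.5 SD shift in one arm, three levels.** Chi-square 58–60%, rank test 70%, rank test with baseline 77% at correlation 0.5 and 86–88% at 0.7. At correlation 0.2–0.3 the three are 56–58%, 68–70% and 70–73%. Taken with step 4, ignoring order costs about 10 to 13 points, and ignoring order and baseline about 13 to 31.

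**6. Limits of the range.**
- Five equal levels, graded shift: the loss from order is about 23–24 points and from both about 27–47 (for example, 38.2% against 62.4% and 85.5% at correlation 0.7).
- Dichotomised items: chi-square and rank test are equal, about 58–60% each at 0.5 SD.
- A 0.3 SD shift: all tests are weak, about 22–24%, 29–31% and 31–35%.

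**7. Type I error.** With three levels and no shift, rejection rates were 3.9–5.1% (chi-square), 4.3–5.1% (rank test) and 4.4–5.4% (rank test with baseline).

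**The case against.** The strongest reply has five parts.

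- **Baseline.** The article does not say that baseline is ignored. It says only that chi-square tests will be used, and the tables could in principle hold change categories. This stands in part: non-use of baseline is the natural reading of a chi-square test outside the repeated-measures list, not an explicit statement.
- **Size.** The document gives no number of levels, distribution, effect or correlation for EQ-5D. A reader might infer that much of the power is lost. The documents do not support that as a general statement: at correlation 0.3 baseline adds only about 1 to 3 points, and the large figures need correlations of 0.5 to 0.7. This stands.
- **Exception.** A reader might infer that EQ-5D alone is denied a longitudinal analysis. That is not so. BMI and hip rotation are also off the repeated-measures list, while the EQ-5D current mental health state scale is on it. This stands.
- **Importance.** EQ-5D is one of eight secondary outcomes. Related constructs are covered by the VAS, Lequesne index, AIMS2, SF-36 and TUG, all analysed as metric. This stands and limits the weight of the point.
- **Interpretation and fix.** Arm percentages show direction, a three-arm rank test gives no effect size either, and the simulations used rank tests, not the proportional-odds model proposed. All true. But a proportional-odds model does give a direction and a size, which chi-square does not.

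None of this removes the core. The article names both the scale level and the test, so this is a stated choice and not detail left to a fuller document.

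**Conclusion.** The point holds as a fault of efficiency and interpretability in one secondary outcome. The EQ-5D items are labelled nominal against the protocol's own description of them and against its own rule on scale level, and the test assigned ignores their order.

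Under three levels, 60 per arm and the shifts examined, the cost is about 10 to 13 percentage points of power for order alone. It is about 13 to 31 points for order and baseline together at latent correlations of 0.3 to 0.7. The first range does not depend on how the baseline question is read; the second does. The loss would be larger with five levels, and order would cost nothing with dichotomised items.

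A reader might go further and call the EQ-5D analysis invalid or the trial underpowered. Neither follows: type I error stays near 5%, and the stated power concerns only the primary outcome.

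**What to change.** In the Statistical analysis section, call the EQ-5D items ordinal and replace the outcome chi-square tests with a proportional-odds model for each item, at discharge and at the ten-week follow-up. Include arm and the patient's baseline level as terms, and report odds ratios with 95% CI. Where levels are sparse, use a rank test stratified by baseline level. Keep chi-square for sex and affected joint.

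The cost is about one sentence of wording. It needs no new data and no further patients. The downside is a proportional-odds assumption that has to be checked.

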### Feasibility of the study design

A pilot study was carried out between June 2008 and January 2009 to check the practicability, the treatment protocols, and the randomisation procedure. Patients were recruited at a specialist clinic in Germany. A total of 30 patients with symptomatic osteoarthritis of the hip or knee joint were randomised into intervention group A (hydrotherapy), intervention group B (physiotherapy) or the control group C (physiotherapy and hydrotherapy). The results of this pilot study showed that all study procedures, therapeutic interventions, and randomisation procedures were practicable and feasible; there was no disqualification on account of unwanted adverse reactions or side effects. All physicians and therapists reported problem-free implementation of the study protocol and efficient study coordination.

## Discussion

The increasing age of the population, particularly in the western world, means that the prevalence of osteoarthritis of the hip and knee is also increasing, with corresponding socioeconomic consequences [40,1]. In the reasons for all visits to a general practitioner in Germany, osteoarthritis of the hip and knee come in places 14 and 34, respectively; they come in the third and ninth places for orthopaedic consultations [41].

Although there is currently no curative intervention, in accordance with US and European guidelines, pharmacotherapeutic and non-pharmacological approaches aim at pain control and the reduction of functional restriction. The development of more efficient, cost-effective, sustainable therapeutic strategies with fewer side effects is thus gaining in significance.

It has been established that hydrotherapy for osteoarthritis of the hip or knee joint using serial cold and warm water stimulation not only improves the range of movement in the affected joint but also provides significant pain relief and increases quality of life over a period of up to three months [11,25]. Even so, there is only scattered evidence from RCTs or meta-analyses which investigate the use of hydrotherapy for osteoarthritis with respect to its long-term and sustained effects [18].

For this reason, we designed this study to evaluate the efficiency of hydrotherapy of the affected joint, in the form of alternate cold and warm Kneipp affusions, in patients with symptomatic osteoarthritis of the hip or knee, in comparison with conventional physiotherapy.

The statistical analysis of the study result will follow the intention-to-treat principle.

The study has limitations, however: hydrotherapy in patients with symptomatic osteoarthritis will be studied in comparison with conventional physiotherapy in the context of a two-week inpatient stay in a well-known German specialist clinic for integrative medicine and centre for hydrotherapy, with ten weeks' subsequent observation. Possible secondary intervention parameters, such as simultaneous sports activity, movement therapy, nutritional therapy or dietary measures for weight reduction of obese patients with osteoarthritis during their inpatient stay were not included in the pilot study, nor will they be in the main study. For one thing, the hydrotherapy will not be continued during the ten week observation phase and, for another, the intake of phytotherapeutics and nutritional supplements will not be studied. These will be the subjects of further RCTs.

However, the results of our pilot study have shown that the study procedures, therapeutic interventions and randomisation procedure are all practicable and feasible. In addition we observed positive long-term effects of the hydrotherapy with respect to pain and quality of life.

This study design is based on the CONSORT statement for randomised, controlled studies [42].
